#### Methods of statistical analysis

The primary efficacy analysis will be based on the intention-to-treat (ITT) population. Sensitivity analyses of the primary endpoint will be based on the per-protocol (PP) set. The primary endpoint will be analyzed by performing multivariable cox-regression adjusting for the variable therapy group and the stratification variables. The two-sided significance level is set to α = 0.05 (two-sided). Secondary endpoint analyses will be performed descriptively. Secondary endpoint analyses for group comparison include t-tests and chi-squared tests for continuous and ordinal or dichotomous variables, respectively. Feasibility will be analyzed by a description of absolute and relative frequencies of treatment withdrawal, which will be compared between treatment groups by chi-squared tests. Safety analysis will be done for all of the patients who received at least one dose of study medication and will comprise a description of relative and absolute frequencies of adverse events, severity grade based on the CTCAE Version 5.0. The adverse event summary tables will provide the number and percentage of patients with adverse events and the 95% Clopper-Pearson type confidence intervals for the event rates.

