• Fully-informed written consent • Confirmed ED SCLC • ECOG performance status score ≤ 1 • Any response after four cycles of induction chemo-immunotherapy defined as CR/PR or thoracic SD with CR/PR of extrathoracic lesions • Thoracic treatment volume considered treatable using acceptable radiation fields as judged by a radiation oncologist • 28 ± 7 days between last administration of chemo-immunotherapy and randomization. • Patients with a history of treated CNS metastases are eligible, if there is no ongoing requirement for corticosteroids as therapy for CNS disease. Patients with asymptomatic brain metastases that do not require local therapy with irradiation (whole brain irradiation) can be included. • No previous radiotherapy to lung and mediastinal lymph nodes within the past 5 years • Availability of pre-treatment tumor tissue specimen • FEV1 ≥ 40% • Adequate bone marrow, renal function, and hepatic functions	• Prior treatment with immunotherapeutic drugs (with the exception of induction chemo-immunotherapy as defined in inclusion criteria) • Prior therapy for limited-stage SCLC with curative intent • History or current radiology suggestive of interstitial lung disease (ILD) (including but not limited to idiopathic pulmonary fibrosis (IPF), formerly described as usual interstitial pneumonia (UIP), and cryptogenic fibrosing alveolitis (CFA)), non-infectious pneumonitis, drug-induced pneumonitis, idiopathic pneumonitis. • Any concurrent cancer treatment or major surgery (as defined by the Investigator) • Active or prior documented autoimmune or inflammatory disorders or history of active primary immunodeficiency • Current use of immunosuppressive medication • Positive testing for hepatitis B virus surface antigen (HBV sAg), hepatitis C virus ribonucleic acid (HCV RNA), or human immunodeficiency virus (HIV) • History of another primary malignancy except for malignancies treated with curative intent and no known active disease ≥3 years before first dose of study medication • Any co-existing medical condition that in the investigator’s judgement will substantially increase the risk associated with the patient’s participation in the study.

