### Study procedures

Before a patient’s involvement in the clinical study, the investigator is under obligation to obtain written informed consent. The randomization will be done by a validated program using variance minimization method [17]. All randomization design aspects and patient allocation statuses underly strict access control. The allocation of the patient numbers and treatment groups will be coordinated by an Interactive Web Response System (IWRS) system integrated in the eCRF. After 1:1 randomization, eligible patients will receive either atezolizumab (1200 mg fixed dose, every 3 weeks [Q3W]) and TRT (30 Gy in 10 fractions) in arm A or atezolizumab only (1200 mg fixed dose, Q3W) in arm B. Patients will be stratified during randomization according to presence of brain metastases (yes vs no), thoracic response after induction therapy (complete/partial response [CR/ PR] vs stable disease [SD]), and prophylactic cranial irradiation PCI (yes vs no). Treatment will be discontinued in case of progressive disease, unacceptable toxicity, on patients’ request, or at the end of study.

In order to ensure patient safety with regard to a potential increase in risk of treatment-related pneumonitis when combining TRT with immune checkpoint inhibition, a safety interim analysis will be performed in arm A after *n =* 23 patients have been followed for 3 months after the end of TRT. If in this cohort the number of patients with a grade ≥ 3 pneumonitis is 2 or more, recruitment to the trial will be stopped. All evaluations will be performed by the medically responsible experts of this trial, i.e. the Coordinating Investigator, the Deputy Coordinating Investigator and the Mentoring Coordinating Investigator– under support of the study statistician as far as applicable. They will provide their opinion to the Sponsor or its delegate who will be responsible for the formal decision on termination / continuation. The Safety Monitoring Committee (SMC) will additionally review all evaluations / decisions and provide its opinion to the Sponsor.

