During treatment, tumor response will be assessed according to Response Evaluation Criteria in Solid Tumors (RECIST), version 1.1 by radiological imaging by computed tomography (CT) and/or magnetic resonance imaging (MRI) of the chest and upper abdomen at baseline, then every 6 weeks for the first 36 weeks, and every 9 weeks thereafter until occurrence of disease progression, according to the standard of care. After treatment discontinuation for reasons other than progressive disease, imaging will be performed accordingly to the above-mentioned schedule until progression, death, initiation of another anti-cancer therapy according to the standard of care or end of study. After the end of study, subjects will be proactively followed up regarding treatment-related adverse events until resolved, returned to baseline or deemed irreversible, until lost to follow-up, or withdrawal of study consent. All patients will be followed for survival. Follow-up by phone every 3 months (every 12 weeks [Q12W] ± 14 days) will be offered to patients who decline to return to the site for evaluations. The investigators of the study are responsible for the further treatment of the patient after the end of the study treatment for disease progression and shall support and advice the patients.

Safety assessment during this trial will include physical examinations, Eastern Cooperative Oncology Group (ECOG) performance status, clinical laboratory profile and continuous assessments of adverse events. The brief summary of all study procedures is presented in Table 2. An electronic case report form (eCRF) will be filled by the principal investigator or authorized study stuff person for each participant for data collection throughout the entire trial. The investigator must obtain written informed consent before patient participates in the clinical study. In addition, an adjudication committee has been established to exclude interstitial lung disease (ILD) in all pre-screened patients prior to study inclusion. All observed toxicities and side effects will be recorded in the eCRF and graded according to National Cancer Institute Common Terminology Criteria for Adverse Events (NCI-CTCAE) v5.0 for all patients and their relationship to all study treatment/ procedures assessed and summarized.

**Table 2 Tab2:** Schedule of assessments

Procedure/ Point in Time	Screening	Treatment				Post- Treatment		

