#### Sample size calculation

With *n =* 104 patients, under the assumption of a 20% improvement (from 52 to 72%) in the 12-month OS rate, a difference between treatment groups with regard to the primary endpoint OS can be detected with a power of 80% using a log-rank test at a two-sided alpha of 5%, assuming a dropout rate of about 10%, follow-up phase of 24 months, and an accrual period of 24 months. This improvement of 20% points corresponds to the effect of the radiation therapy together with the one mediated by ICI [2, 6]. Based on these assumptions, the resulting total sample size yielding the necessary number of 66 events is 92 patients (46 per arm) to achieve a power of 80%. In order to adjust for dropouts, *n =* 104 patients have to be randomized.

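### Baseline ECOG status (0 vs 1) could be pre-specified as a further covariate in the primary OS Cox model: an inexpensive improvement to a valid analysis

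*Protocol article*

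**What the plan says.** Under Methods of statistical analysis, the article fixes the primary OS model: "The primary endpoint will be analyzed by performing multivariable cox-regression adjusting for the variable therapy group and the stratification variables". The factors are listed under Study procedures: "Patients will be stratified during randomization according to presence of brain metastases (yes vs no), thoracic response after induction therapy", followed by PCI (yes or no). Allocation is 1:1 by minimisation.

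ECOG is in neither list. Table 1 restricts entry to "ECOG performance status score ≤ 1", so two values are possible. Study procedures names "Eastern Cooperative Oncology Group (ECOG) performance status" among the safety assessments, and Table 2 schedules it at screening, on day 1 of cycle 1, at each cycle and at end of treatment. A baseline value is therefore planned for every patient.

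The only sensitivity analysis of OS that the article describes repeats the analysis in the per-protocol set. The sample size section plans "under the assumption of a 20% improvement (from 52 to 72%) in the 12-month OS rate", with 66 events, 92 evaluable and 104 randomised patients for 80% power, using a two-sided 5% log-rank test.

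**The concern.** If ECOG 0 vs 1 is prognostic for OS in these patients, leaving it out of a Cox model has two effects. The estimated treatment hazard ratio moves slightly towards 1, with some loss of power. And because ECOG is not a minimisation factor, its balance across about 46 to 52 patients per arm is left to chance, and the stated model cannot correct a difference that arises.

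At stake is some efficiency, and how well the estimate can be defended in the one trial that will be run. The trial is open-label, so an ECOG adjustment first chosen once results by arm are known would carry little weight. It helps only if fixed in advance.

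**Working it through.** **1. The plan's own figures.** Inputs from Sample size calculation: 12-month OS 52% vs 72%, two-sided alpha 0.05, power 80%, 24 months of accrual, 24 months of follow-up, about 10% dropout. Allocation is 1:1.

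- Hazard ratio under exponential survival: ln(0.72)/ln(0.52) = 0.502.
- Events (Schoenfeld): (1.960 + 0.842)² / (0.25 × [ln 0.502]²) = 66.2, against 66 stated. Power at 66 events is 79.9%.
- Event probability with uniform accrual: 0.849 (control) and 0.620 (radiotherapy), mean 0.735. N = 66.2/0.735 ≈ 90, or 67/0.735 ≈ 91, against 92 stated. At N = 92 about 67.6 deaths are expected.
- Dropout: 92/0.90 = 102.2, rounded up to 103, against 104 stated.

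The figures reproduce within rounding, from a log-rank calculation that assumes no gain from covariates.

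**2. Power with and without ECOG.** The ECOG hazard ratio and the share with ECOG 1 are assumptions. Three simulation set-ups were used, each with 92 patients, exponential survival, 24 + 24 months and a treatment hazard ratio of 0.502 given ECOG.

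- Set-up A: ECOG 1 share 35% or 60%, 3,000 trials per cell, stratification factors not simulated.
- Set-up B: share 55%, 10,000 trials per ECOG effect, minimisation on the three factors, each with an assumed hazard ratio of 1.3.
- Set-up C: a separate run, share 55%.

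| ECOG HR (assumed) | A: without / with | B: without / with | C: without / with |
|---|---|---|---|
| 1.0 | 79–80% / 79–80% | not run | 81% / 80% |
| 1.3 | 79–80% / 80–81% | 78.7% / 79.3% | 81% / 82% |
| 1.5 | 77–80% / 79–81% | 79.0% / 79.9% | 77% / 79% |
| 1.8 | not run | 76.7% / 79.7% | not run |
| 2.0 | 74–76% / 78–80% | 74.2% / 78.9% | 73% / 78% |

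The gain is about 0 to 2 points up to an ECOG hazard ratio of 1.5, 3 points at 1.8, and about 4 to 5 at 2.0. At 2.0 the average estimated treatment hazard ratio is about 0.52 without ECOG and 0.50 with it in set-up A, and 0.51 and 0.49 in set-up B.

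**3. Type I error.** With no treatment effect, rejection rates without / with ECOG were 5.3% / 5.4% (ECOG hazard ratio 1.5) and 4.9% / 5.1% (2.0) in set-up A. In set-up B both models rejected in about 5.4 to 5.9% of trials. Neither model has an advantage here.

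**4. Chance imbalance.** With 46 per arm and 55% ECOG 1, the SD of the difference in prevalence is √(0.55 × 0.45 × 2/46) = 0.10. In set-up A, a difference of at least 10 points occurred in about 32 to 36% of trials, and of at least 15 points in about 15 to 18%. To first order, a 15-point imbalance shifts the log hazard ratio by 0.15 × ln(ECOG hazard ratio):

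- ECOG hazard ratio 1.5: 0.15 × 0.405 = 0.061, a factor of 1.06.
- ECOG hazard ratio 2.0: 0.15 × 0.693 = 0.104, a factor of 1.11.

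For scale, the standard error of the log hazard ratio with 66 deaths is about 2/√66 = 0.246, so significance needs an estimate of about exp(−1.96 × 0.246) = 0.62 or lower. An estimate of 0.60 would become 0.60 × 1.06 = 0.64 or 0.60 × 1.11 = 0.67.

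**5. Room in the model.** Treatment, three stratification variables and ECOG make five terms: 66/5 ≈ 13 deaths per term.

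**The case against.** The strongest reply is that nothing is wrong. The factors balanced at randomisation are the factors in the model, which is a standard, pre-specified choice. That stands.

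The article also nowhere says that ECOG 0 vs 1 predicts OS among patients already selected for good performance status and response to induction. That stands too, and is why the range starts at an ECOG hazard ratio of 1.0, where there is no gain.

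A sharper objection concerns the simulations. The plan's 52% vs 72% describes whole arms, so 0.502 is a marginal hazard ratio. Using it as the effect within ECOG levels weakens the marginal effect and then blames the stated model for the loss. This is fair in part. With the simulation calibrated so that the arms as a whole have 52% and 72% survival at 12 months, power at an ECOG hazard ratio of 2.0 is 75% without and 80% with ECOG, compared with 73% and 78% before. The power without ECOG rises, but the gain remains.

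Random imbalance is already allowed for in the test's error rate. That is true over repeated trials, and validity is not in question. Adjustment serves the estimate in the trial actually run.

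Finally, the SAP is not shown and may contain an ECOG-adjusted analysis. It could, but the article itself states the covariates of the primary model.

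A reader might infer that the trial is underpowered or its 80% miscalculated. The documents do not support that: the figure reproduces without any covariate gain. Nor does the point carry over to PFS, because the article makes secondary analyses descriptive and states no Cox model for PFS.

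**Conclusion.** The point holds as an improvement to a stated analysis choice, not as an error or contradiction. Leaving ECOG out neither biases the test nor inflates type I error. It leaves a small gain in power unused and a possible chance imbalance uncorrected.

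The size depends on two quantities that the article does not give, the prognostic effect of ECOG and the share with ECOG 1. If ECOG has little effect on OS, almost nothing is gained; the benefit becomes material only towards the upper end of the assumed range. The protection against imbalance is the better reason for the change, since a sizeable imbalance is not rare at this sample size and could matter for an estimate near the significance boundary.

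**What to change.** Pre-specify baseline ECOG performance status (0 vs 1, screening value) as an additional covariate in the primary OS Cox model, beside therapy group and the three stratification variables. Fix this before any look at OS by arm. Report the model with stratification variables only as a sensitivity analysis.

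The cost is one sentence in the protocol or SAP and one term in the program. No new data collection or change to the sample size is needed.

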**Methods/design:**

The TREASURE trial is a randomized, multicenter, phase II clinical trial (ClinicalTrials.gov identifier, NCT04462276). One hundred four patients suffering from extensive disease (ED) SCLC, with any response to the standard of care induction chemo-immunotherapy will be randomized to receive atezolizumab maintenance therapy with or without TRT. The primary endpoint of this study is overall survival (OS). Secondary endpoints include further measures of efficacy, safety, and the collection of biomarker samples. A safety interim analysis will take place after *n* = 23 patients receiving TRT have been observed for three months after the end of TRT.

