### Study endpoints

The primary endpoint of the TREASURE trial is OS defined as time from randomization to death due to any cause. Secondary efficacy endpoints include 1- and 2-year OS rates, PFS, response rate, and the intrathoracic tumor control defined as rate of intrathoracic progression and time to intrathoracic progression. Moreover, safety will be assessed by evaluating the incidence, nature, causal relationship and severity of adverse events according to CTCAE v5.0 (with special focus on pulmonary events including pneumonitis; hepatic, gastrointestinal, endocrine, ocular, dermatologic, renal and pancreatic events including pancreatitis; immune-mediated myocarditis and myositis as well as infusion-related reactions and cytokine-release syndrome) and the frequency of abnormal laboratory parameters, and feasibility will be addressed in terms of frequency of treatment withdrawal, i.e. due to adverse events or other reasons, and completion of radiotherapy. Furthermore, cancer-related quality of life will be measured using the Functional Assessment of Cancer Therapy – Lung (FACT-L) questionnaire. The planned biomarker analysis of biomaterials that will be collected during the clinical trial is an exploratory endpoint of the TREASURE study.

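### The plan assigns chi-squared tests to ordinal secondary variables; an ordinary chi-squared test ignores category order and loses power against an ordered shift (minor; mainly relevant to CTCAE grade)

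*Protocol article*

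**What the plan says.** The Protocol article, Methods of statistical analysis, pairs types of variable with tests for the secondary comparisons: "Secondary endpoint analyses for group comparison include t-tests and chi-squared tests for continuous and ordinal or dichotomous variables, respectively". Ordinal and dichotomous variables share one test. No rank or trend version is named, and no reason is given for setting the order aside. The same paragraph says of these analyses: "Secondary endpoint analyses will be performed descriptively".

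Three other statements decide which variables the sentence can reach.

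- Study endpoints makes severity part of the safety assessment: "safety will be assessed by evaluating the incidence, nature, causal relationship and severity of adverse events according to CTCAE v5.0". CTCAE grade is an ordered scale.
- The safety sentence in Methods of statistical analysis "will comprise a description of relative and absolute frequencies of adverse events, severity grade based on the CTCAE Version 5.0". It adds Clopper-Pearson intervals for event rates and names no between-arm test of grade.
- For efficacy, Study endpoints says: "Secondary efficacy endpoints include 1- and 2-year OS rates, PFS, response rate, and the intrathoracic tumor control". Response appears as a rate, a yes/no variable. Study procedures says only how response is measured: "tumor response will be assessed according to Response Evaluation Criteria in Solid Tumors (RECIST), version 1.1".

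**The concern.** On a table of 2 arms by k ordered categories, the ordinary (Pearson) chi-squared test has k − 1 degrees of freedom. It gives the same p-value if the categories are shuffled. For a graded outcome the natural question is whether one arm is shifted towards higher grades. A test with one degree of freedom that uses the order puts its power on that question; the general chi-squared test spreads it over every possible pattern of difference.

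The outcome most exposed is adverse-event severity. The article treats excess pneumonitis under combined treatment as its main safety worry, and about 52 patients per arm leave little power to spare. If grade is compared between arms with the named test, a real ordered shift in arm A is less likely to give a small p-value than the same data would with a rank or trend test.

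**Working it through.** **Inputs from the article.** The Methods/design paragraph of the Abstract gives the total: "One hundred four patients suffering from extensive disease (ED) SCLC" will be randomized. Study procedures gives the ratio: "After 1:1 randomization, eligible patients will receive" one of two regimens. So n = 104 / 2 = 52 per arm. A two-sided 5% level is used here, as for the primary endpoint.

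**The plan's own figures.** The article gives no power, effect size or category distribution for any ordinal variable, so there is no stated figure on this point to reproduce. The primary sample size does reproduce:

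- HR = ln 0.72 / ln 0.52 = 0.502.
- Schoenfeld events = 4 × (1.960 + 0.842)² / (ln 0.502)² = 4 × 7.849 / 0.474 = 66.2, against 66 stated.
- 46 / 0.9 = 51.1, rounded up to 52 per arm, or 104 in total.

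**Step 1: cost of the extra degrees of freedom.** No category distribution is needed. A 1-df test has 80% power at noncentrality λ = (1.960 + 0.842)² = 7.849. Power of a k-category chi-squared test carrying the same signal is P[χ²(k − 1, λ) > 95th percentile of central χ²(k − 1)].

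| Categories | df | Critical value | Power |
|---|---|---|---|
| 2 | 1 | 3.841 | 80.0% |
| 3 | 2 | 5.991 | 70.9% |
| 4 | 3 | 7.815 | 64.5% |
| 5 | 4 | 9.488 | 59.5% |

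The loss is 0, 9, 16 and 20 points respectively. With two categories there is none.

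**Step 2: simulation at 52 per arm.** The category distributions and odds ratios are assumptions. One arm has the distribution shown. In the other, every cumulative odds is changed by the same factor OR (proportional odds). There were 40,000 runs per setting. Each cell gives Pearson chi-squared power / tie-corrected Wilcoxon power, in %.

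| Assumed distribution (%) | OR 1.5 | OR 2 | OR 2.5 | OR 3 | OR 4 |
|---|---|---|---|---|---|
| 30/40/30 | 15.3 / 19.9 | 37.7 / 47.4 | 59.1 / 69.6 | 75.5 / 84.1 | 91.7 / 95.8 |
| 10/40/30/20 | 13.1 / 20.4 | 32.3 / 47.7 | 52.6 / 70.4 | 69.6 / 84.7 | 88.9 / 96.1 |
| 30/30/25/10/5 | 11.4 / 20.7 | 27.9 / 48.0 | 47.8 / 71.1 | 64.8 / 85.2 | 85.7 / 96.2 |
| 10/20/30/25/10/5 | 10.5 / 20.9 | 26.1 / 50.0 | 45.9 / 73.7 | 63.4 / 87.1 | 85.9 / 97.4 |

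The smallest loss is 95.8 − 91.7 = 4.1 points (3 categories, OR 4). The largest is 73.7 − 45.9 = 27.8 points (6 categories, OR 2.5). A linear trend test with equal scores came within about 3 points of Wilcoxon throughout.

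**Step 3: a sparse scale such as pneumonitis grade.** Assume 90/4/4/2% for grades 0, 1, 2 and ≥ 3 in arm B. Only the 2% comes from the article (the non-toxicity scenario under Interim safety analysis). At OR 3, odds of grade ≥ 3 in arm A are 3 × 0.02 / 0.98 = 0.061, a rate of 5.8%. Power is about 33% for chi-squared and 53% for Wilcoxon. With no difference between arms, chi-squared rejects about 2.3% of the time and Wilcoxon about 5%.

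**Step 4: where the order does not help.** For two assumed four-category differences that are not monotone, chi-squared had the higher power:

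- 10/40/30/20 against 10/60/10/20: 63% against 27% for Wilcoxon.
- 5/25/40/30 against 15/25/20/40: 59% against 6%.

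**The case against.** The strongest reply is that the article never says an ordered variable will be tested between arms. Safety has its own sentences, which tabulate grade and give intervals. The feasibility sentence just before them does name a between-arm test, and the contrast suggests that grade is only described. This largely stands: a test of grade is an inference from the general sentence and the endpoint list. But the general sentence uses the word ordinal, so it foresees at least one such comparison. If none is intended, the word should go.

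Second, chi-squared test could mean a Mantel-Haenszel trend version, which has one degree of freedom. The article does not exclude this. But one name covers ordinal and dichotomous variables alike, so the ordinary reading is the Pearson test. If a trend version is meant, saying so is the same one-line edit. Nor is this a detail simply left to a fuller document: the article states the choice of test.

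Third, the analyses are descriptive and unpowered. This stands and limits the weight of the point.

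A reader might go further and infer three things that the article does not support:

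- *That RECIST response categories will be compared by chi-squared.* The endpoint is a response rate, for which the test is suitable and the loss is zero.
- *That a fixed number of power points is lost.* Every such figure rests on assumed distributions and effect sizes, and the sign can reverse.
- *That a shift in toxicity would go unseen.* The planned counts, percentages and intervals would still show its direction and size.

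**Conclusion.** The point holds in a narrow form. The article assigns ordinal secondary variables to a test that, as ordinarily understood, discards their order, and it gives no reason. The one listed component clearly affected is CTCAE severity grade, and only if grade is in fact compared between arms under the general sentence.

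The 4-to-28-point range in the simulations assumes a common odds ratio across categories, which favours the rank test. The degrees-of-freedom figures likewise assume that the 1-df test captures the whole difference. Neither is a property of the plan.

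The impact is minor. The primary overall survival analysis does not use this test. The interim pneumonitis rule counts grade ≥ 3 cases in arm A alone and is also unaffected.

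**What to change.** Reword the sentence so that t-tests apply to continuous variables, a Wilcoxon rank-sum or Mantel-Haenszel (linear trend) test applies to any ordinal variable compared between arms (such as worst CTCAE grade per patient), and chi-squared tests apply to dichotomous variables. If no ordinal variable is to be tested, delete the word ordinal instead. Response rate and other yes/no summaries stay as they are.

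The cost is one sentence and a standard SAS procedure, with no new data, visits or patients. The downside is lower sensitivity to a difference that is not monotone across categories. The frequency tables already planned would still show such a pattern.

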	Inclusion	C1D1	Each cycle (q2w ± 3 days)	Every second cycle (q4w ± 3 days)	EOT	Safety FU-1*	Safety FU-2**	FU (q12w ± 14 days)
Central review – ILD exclusion^#^	(x)							
Informed consent, eligibility criteria, demographics, medical and disease history	x							
Prior and Concomitant Medication Review	x	x	x		x			
Allocation/Randomization	x							
Vital Signs, O_2_ Saturation, and Weight	x	x	x		x	x	x	
ECOG Performance Status	x	x	x		x			
Pregnancy Test, CBC with Differential, Serum Chemistry Panel, Thyroid function test	x	x	x		x			
Urinalysis	x	Whenever clinically indicated						
12-lead ECG	x	Whenever clinically indicated						
Pulmonary function tests	x	x^a^		together with staging	x	x	x	
AEs	x	x	x		x	x	x	x
Full Physical Examination	x							
Directed Physical Examination		x	x		x	x	x	
FACT-L questionnaire	x	x		x	x	x	x	(x)
Tumor Imaging	x	(x^b^)		(x^c^)	(x^d^)			(x^d^)
Tissue	x	Optional: Re-Biopsy at time of progression						
Blood and stool	x	(x^e^)	x	x	x			
Atezolizumab administration		x	x					
Radiotherapy (Arm A^f^)		x						

^#^: A sponsor-independent adjudication committee was established to exclude interstitial lung disease (ILD) [Excl. criterion 5] in all pre-screened patients prior to study inclusion. All study sites are encouraged to provide tumor imaging in pseudonymize form during the (pre-)screening phase for the central review process

*: The regular 30-day full safety follow-up period (FU-1) begins on the day after the EOT visit and lasts approximately 30 days. The FU-1 visit occurs at or near the end of the 30-day safety follow-up period (±7 days)

**: The regular 90-day full safety follow-up period (FU-2) begins on the day after the EOT visit and lasts approximately 90 days. The FU-2 visit occurs at or near the end of the 90-day safety follow-up period (±7 days)

^a^: To be performed on C1D1 if in accordance with local standard

^b^: Chest X-ray to be performed on cycle 1 if in accordance with local standard

^c^: First on-study imaging to be performed 6 weeks (± 7 days) after baseline imaging. Further on-study imaging to be performed Q6W (42 days ±7 days) for the first 36 weeks, and every 9 weeks (±7 days) thereafter until occurrence of disease progression, according to the standard of care

^d^: Only applicable if EOT not according to already detected disease progression

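### The only test named for continuous secondary endpoints is the t-test; for FACT-L it is less precise than a baseline-adjusted comparison of data already collected

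*Protocol article*

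**What the plan says.** In the protocol article, Methods of statistical analysis, one sentence covers between-arm comparisons of secondary endpoints; they are said to include "t-tests and chi-squared tests for continuous and ordinal or dichotomous variables", in that order. The sentence before it sets their status: "Secondary endpoint analyses will be performed descriptively". The same section specifies the primary survival analysis as "multivariable cox-regression adjusting for the variable therapy group and the stratification variables".

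Under Study endpoints, "cancer-related quality of life will be measured using the Functional Assessment of Cancer Therapy – Lung (FACT-L) questionnaire". The other secondary endpoints listed there are rates, times to an event, or frequencies of adverse events, laboratory abnormalities and withdrawals. FACT-L is therefore the endpoint to which the t-test clause most plainly applies.

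Table 2 (Study procedures) schedules the "FACT-L questionnaire" at screening, C1D1, every second cycle, end of treatment and both safety follow-up visits, with a bracketed mark at the 12-weekly follow-up. The article names no score, analysis visit, covariate or longitudinal model for FACT-L.

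**The concern.** A two-sample t-test takes one number per patient and no covariates. FACT-L has at least one score before treatment and several after it, and patients differ in quality of life before they start. Part of the spread in follow-up scores is therefore predictable from a score already in the database. A t-test either leaves that predictable part in the error term (follow-up scores) or removes it with a fixed weight of one, which is generally not the best weight (change scores).

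The trial adds radiotherapy to maintenance immunotherapy, and the Discussion accepts some overlap in their toxicities. FACT-L is the patient-reported side of that trade-off. With 104 patients randomized and fewer providing scores as time passes, an unnecessarily wide interval makes it harder to say whether adding radiotherapy helps or harms quality of life.

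**Working it through.** **What the plan gives.** There is no FACT-L figure to reproduce: the article states no standard deviation, target difference, correlation or power for it. The only sample-size figures concern survival (Sample size calculation), and they reproduce. HR = ln(0.72)/ln(0.52) = 0.502. Schoenfeld's formula gives 67 events against 66 stated, and 66 events give 79.9% power. The 46 patients per arm from that section are used below for illustration only.

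**Assumptions not in the document.** The correlation rho between baseline and follow-up FACT-L is taken as 0.4 to 0.7. The SD is assumed equal at baseline and follow-up. Data are complete at one visit.

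**Variance of the arm difference**, relative to a t-test on follow-up scores:

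- t-test on follow-up scores: 1
- t-test on change from baseline: 2(1 − rho)
- ANCOVA adjusting for baseline: 1 − rho²

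For 0 < rho < 1, ANCOVA is below both. First, 1 − rho² < 1. Second, (1 − rho²)/[2(1 − rho)] = (1 + rho)/2 < 1. The reduction is rho² against the follow-up-score test and (1 − rho)/2 against the change-score test.

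| rho | Follow-up t-test | Change t-test | ANCOVA | Cut vs follow-up | Cut vs change | Cut vs better t-test |
|---|---|---|---|---|---|---|
| 0.4 | 1 | 1.20 | 0.84 | 16% | 30% | 16% |
| 0.5 | 1 | 1.00 | 0.75 | 25% | 25% | 25% |
| 0.6 | 1 | 0.80 | 0.64 | 36% | 20% | 20% |
| 0.7 | 1 | 0.60 | 0.51 | 49% | 15% | 15% |

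At rho = 0.7 the variance remaining is 0.51, so the cut is 1 − 0.51 = 0.49.

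**In patients.** Matching ANCOVA's precision needs 1/(1 − rho²) = 1.19 to 1.96 times as many patients with a follow-up-score t-test. With a change-score t-test it needs 2/(1 + rho) = 1.43 to 1.18 times as many.

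**In power, as illustration.** Assume a true difference of 0.5 SD and 46 per arm. Power = Φ(0.5 × √(46/2)/√v − 1.96), where v is the relative variance above, and 0.5 × √23 = 2.398.

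| rho | Follow-up t-test | Change t-test | ANCOVA |
|---|---|---|---|
| 0.4 | 66.9% | 59.1% | 74.4% |
| 0.5 | 66.9% | 66.9% | 79.1% |
| 0.6 | 66.9% | 76.5% | 85.0% |
| 0.7 | 66.9% | 87.2% | 91.9% |

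Fewer patients will have scores at later visits, so every absolute power would be lower there. The variance ratios do not depend on the number of patients.

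**Repeated visits.** Using several post-baseline scores can add precision, but the amount depends on how many scores are observed and why others are missing. Under complete data and equal correlations, two follow-up visits averaged and baseline-adjusted at rho = 0.5 would have relative variance (1 + 0.5)/2 − 0.25 = 0.50. Those conditions will not hold here, so the conclusion does not rest on this figure.

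**The case against.** **The analysis criticised is partly inferred.** The sentence is generic, uses a verb that is not exhaustive, and does not name FACT-L. It cannot describe every secondary analysis, since progression-free survival and time to intrathoracic progression need other methods. A reader might infer that the plan ignores the baseline score and compares arms one visit at a time among those still responding. The article says neither. A t-test on change fits its wording and uses the baseline. A reader might also take the 49% reduction, or nearly twice as many patients, as the cost of the plan. That holds only for a raw follow-up-score test at the highest assumed correlation. This objection stands, and it limits the claim to what is true under both readings.

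**Model detail belongs in the analysis plan.** An article need not give covariates and visits, and their absence alone would be no finding. But the article does name a method for continuous endpoints, and a better one is available from the same data. If the analysis plan already specifies it, the sponsor need only confirm this.

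**The analysis is descriptive.** FACT-L carries no hypothesis or power claim, so the point is minor. A descriptive estimate still benefits from a narrower interval, and the primary analysis already uses covariate adjustment.

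**A mixed model does not cure dropout.** This is correct. It assumes data missing at random and, unless its target is stated, implicitly carries scores beyond death. End of treatment and the two safety follow-ups are also timed from the end of treatment, so they are not common visits since randomization. The benefit claimed here is precision, not removal of bias from progression or death.

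**Conclusion.** The point holds as a minor improvement to a secondary, descriptive analysis. The t-test is the only method the article names for continuous secondary endpoints, and for FACT-L it is less precise than baseline adjustment whichever score enters it. The direction follows from the formulas for any correlation between 0 and 1, given equal SDs at baseline and follow-up. The size rests on the assumed range of 0.4 to 0.7. About 15% to 25% of the variance is the fair figure, because it compares ANCOVA with the better t-test at each correlation. The documents do not support saying that the plan discards the baseline or commits to visit-wise testing. The survival analysis, its sample size and its conclusion are untouched.

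**What to change.** In the analysis plan, replace the t-test for FACT-L with ANCOVA at one pre-named on-treatment visit timed from randomization. Adjust for the baseline score and the three stratification factors (brain metastases, thoracic response after induction, PCI). Report the adjusted difference with its 95% CI.

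State whether screening or C1D1 is the baseline. Table 2 marks FACT-L at both and places allocation in the screening column, so in this open-label trial a C1D1 score may be given after the arm is known.

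Alternatively, fit a mixed model for repeated measures over the on-treatment visits, with treatment, visit, treatment-by-visit and the same covariates. State that the estimate refers to patients while alive and assumes data missing at random. In either case, summarise end of treatment and the two safety follow-ups separately.

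Before naming a visit, reconcile the cycle lengths. Table 2 heads its cycle columns q2w and q4w, while Study procedures gives atezolizumab every 3 weeks, and these set the FACT-L visit times.

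The cost is analysis-plan wording and a little more analysis work. No new patients, visits or data are needed.
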